### Intervention

Nurses on a master’s level (APN) are supposed to work as case managers and utilize their advanced nursing expertise. They are employed at the ESA for this study. They will take on all basic functions of case management: gatekeeping, brokering, and advocacy [48]. The intervention focuses on prevention and healthcare promotion for people with intellectual disabilities. It targets four areas of prevention, because the legally determined guideline for prevention in Germany identifies these as aspects to be dealt with in the foreground. Additionally, problems in this area are quite prevalent in people with intellectual disabilities:MobilityNutritionStressAddiction

We do not emphasize the differentiation between primary, secondary, or tertiary prevention, as the boundaries are sometimes blurred [49].

The intervention consists of four home visits over the span of 1 year by APNs. Prior to the visits, a social space analysis [50] is carried out for each of the seven Hamburg districts by the APNs to map out the existing service structure and identify gaps or accumulations. This will serve as a starting point for networking with the service providers as well as an orientation point for being able to refer the clients to suitable service providers with regard to the brokering and gatekeeping element of case management. Additionally, the analysis shows the need to conceptualize further consultation interventions, which have to be offered by the APNs themselves. For each district 1–2 APNs will be employed depending on the size of the population in the respective district.

The first home visits consist of the building of a professional relationship between the clients, their caregivers, and the APNs as well as a first screening of existing and potential health problems and resources. They are going to employ biographic interviews to explore important contextual information [51]. The language level will vary from basic to advanced depending on the client’s abilities. Rules of cooperation are agreed upon, and organizational and time-related issues are resolved. This is especially important from a study operations perspective. Participants in studies can sometimes get confused with the evaluation part of the study and the interventional part. It is helpful to explain the different parties and their roles in the study.

The second visit also takes place within the first month of participation and consists of a detailed assessment of health problems based on the InterRAI intellectual disability assessment [52]. A network map will be drawn to illustrate the social network of the participants. Further differentiated assessments will be used on a case-by-case level. In the aftermath, nursing problems and goals will be structured according to the ABEDL-model [53], and a case description will be prepared.

The third visit takes place in the second month and aims for the development of a prevention plan. In the prevention plan individual goals, (possible) health problems, preventive interventions, and actions to improve health as well as suitable outcomes to measure for evaluation will be formulated on the basis of the aforementioned assessments. The plan will be developed in a joint work between the client, the primary caregivers, and the APN. The fourth visit will happen after 1 year and is supposed to serve for the evaluation of the actions from the prevention plan. Moreover, overarching goals for the client's health beyond the project should be defined together with the clients and their caregivers.

Between the home visits the APNs hold liaison with the clients via their preferred ways, e.g., telephone, e-mail, or video conference. Every 2 months, the prevention plan is going to be reviewed and updated if necessary. Since it is common that people with intellectual disabilities have problems with enrolling in healthcare programs, the APNs will exercise brokering and advocacy to support them in getting the care they need. They will also gatekeep on certain interventions, if those interventions are not primarily needed. The APNs will perform single person interventions in form of counseling regarding the four areas of prevention by themselves, e.g., counseling on stress reduction if there are no suitable interventions available but will of course focus on brokering to keep it manageable. After 6 months, an individual video will be sent to the client, which focuses on motivation and resilience to keep the clients on track of their prevention plan or prompt contacts, if something is not going according to plan.

The APNs document their work in a standardized documentation system.

The CG will receive usual care. The topic of prevention and health promotion is not well covered by the existing practice and therefore we opted not to offer an active intervention. The APNs will not initiate any interaction with participants from the CG. However, because the APNs are situated right within the seven districts in offices open to the public, it cannot be excluded that control patients could receive advice or counseling on healthcare problems.

To improve adherence to the intervention, detailed intervention descriptions were developed for each home visit. However, due to the nature of this communicative, educational, coordinating complex intervention, a degree of flexibility is needed to tailor the intervention to the needs of individuals in this diverse population.

### Outcomes and data collection

Overall, the study consists of six time points (*t*_0_ to *t*_5_) and is illustrated in Table 1. The outcome evaluation will take place from *t*_0_ to *t*_2_ after 12 months. The process evaluation will take place at *t*_3_ after 13 months in the IG. We chose the additional timepoint, because simultaneous collection of outcome and process data would have compromised the rater’s blinding. The process evaluation in the waiting list group will take place at *t*_4_ after 18 months (6 months after receiving the intervention) and *t*_5_ after 24 months (12 months after receiving the intervention). The process evaluation is conducted with all participants and their primary caregivers.

The primary outcome of the study is the health status after 12 months (*t*_2_) measured with the 36-item WHODAS 2.0 interviewer version [54] (proxy). Secondary outcomes are:Health status after 6 months (*t*_1_) measured with 36-item WHODAS 2.0 (proxy)Resilience after 6 (*t*_1_) and 12 (*t*_2_) months measured with RS-11 [55] (self-assessed)Health-related quality of life after 6 (*t*_1_) and 12 (*t*_2_) months measured with the EQ5D-VAS [56] (proxy and self-assessed)

We will use the German version for all outcome measures.

The raters all have a background in nursing or social pedagogy. They will be trained in structured interviewing of people with intellectual disabilities as well as the respective assessments used. A pretest has been performed.

Data collection for outcome evaluation is planned as face-to-face interviews based on a questionnaire consisting of the aforementioned outcome measures as well as date of birth and data collection, sex, living situation, support through formal or informal care, and the rater’s assessment of the potential study group assignment of the participants including justification to check the blinding procedure. Data collection will be conducted in the participants’ homes or a place of their choice. This can be, for example, their own flat, a residential living group, or a residential facility. A primary caregiver (legal representative, family member or professional caregiver) is going to be present for the evaluation of the health status as well as the quality of life. This usually has the beneficial side effect that many participants feel more comfortable with their caregivers present and they can help them in clarifying questions, because they are familiar with their context, e.g., if you want to know whether the person is able to walk one kilometer the concept of 1 km is sometimes difficult to grasp. It is easier, if a caregiver can give an example of something that is as far away, e.g., a supermarket.

Data collection for the process evaluation is also planned as face-to-face interviews and is directed towards the clients as well as their primary caregivers. The questionnaire comprises of questions on the number of contacts, quality of communication between the APN and clients and caregivers, quality of collaboration, the professional relationship, satisfaction with the intervention, if new knowledge has been gained through the intervention on stress, mobility, nutrition, and addiction, and finally potential for improvement of the intervention. In our previous study on medication management of people with intellectual disabilities, it has proven useful to first ask dichotomous questions, e.g., “were you satisfied with the caregivers?” and then to ask on an ordinal scale how (un-)satisfied they were. We will employ this approach throughout the questionnaire.

We will promote participant retention through several steps:Personal telephone contact with participants for scheduling data collection and intervention visitsData collection reminders a week before data collection via cell phone text serviceIntervention reminders a week before the visit via cell phone text servicePossibility of short-term appointment postponements (if within the time frame of data collection and intervention)

We will not collect any further outcome data from the individuals after study dropout. After discontinuation of the intervention, e.g., due to the participant’s request, we will continue to collect all outcome data up to *t*_3_.

### Data processing and analysis

Data will be transferred from the questionnaires to a prespecified data matrix in IBM SPSS Version 27 by two raters simultaneously based on a codebook of variables and their values. Data will be checked periodically by the project lead on double entries, wrong values, and missing questionnaires throughout the process to ensure data quality.

All outcomes can be analyzed with methods for continuous outcomes. We will perform an ANCOVA with the respective outcome at the respective time point (*t*_1_, *t*_2_) as the dependent variable and the baseline value (*t*_0_) as the covariate. We are going to test three hypotheses with a Bonferroni adjusted alpha of 0.025 each:

The IG differs from the CG regarding:The health statusThe health-related quality of lifeResilience

We will use intention-to-treat analysis for people dropping out of the study, if we have any data on them as well as participants discontinuing the intervention.

The process evaluation will be analyzed with descriptive statistics, reporting absolute and relative frequencies as well as measures of central tendency and dispersion suitable for the respective data level of the items.

Sample size calculation has been performed with the software G*power 3.1 [57]. Based on an effect size of *f* = 0.23 for an ANCOVA, a significance level of 0.05 with Bonferroni correction to 0.025, and a power of 0.8, 184 participants have to be recruited. As a conservative decision, we estimated a 30% dropout rate due to the complexity of the intervention and the 1-year time frame as well as the specifics of the target population. Therefore, we plan to include 256 people with intellectual disabilities (128 per group) in this study.

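### Three hypotheses are each tested at 0.025 as a Bonferroni correction of 0.05, but the value for three is 0.0167, so the family-wise error can reach 0.075; the primary test alone is not inflated

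*Protocol article*

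**What the plan says.** Under Data processing and analysis, the Protocol article specifies an ANCOVA for each outcome at 6 months (t1) and at 12 months (t2), adjusted for the baseline value. It then says: "We are going to test three hypotheses with a Bonferroni adjusted alpha of 0.025 each". The list that follows opens with "The IG differs from the CG regarding" and names health status, health-related quality of life and resilience. The sample size paragraph of the same section gives the starting level and the result: "a significance level of 0.05 with Bonferroni correction to 0.025, and a power of 0.8, 184 participants have to be recruited".

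Under Outcomes and data collection there is one primary outcome: "The primary outcome of the study is the health status after 12 months", measured with the proxy WHODAS 2.0. The secondary outcomes are WHODAS at 6 months, RS-11 at 6 and 12 months, and EQ-VAS at 6 and 12 months. The EQ-VAS is collected both by proxy and by self-report. The article describes no testing order or gatekeeping, and does not explain why 0.05 is divided by two when three hypotheses are listed.

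**The concern.** The sentence attaches a Bonferroni label to a level that is not the Bonferroni level for the number of hypotheses it counts. Three tests at 0.025 do not hold an overall 0.05. A statement that the intervention affects at least one of the three outcome domains would then carry a higher false-positive rate than the article implies, and a positive secondary result would be open to challenge.

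The plan also names a single primary outcome but places it in a shared-alpha family with the secondary outcomes. A single primary needs no split of 0.05. As written, the primary is tested more strictly than necessary, yet the family for which that was done is not controlled at 0.05.

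**Working it through.** **Inputs** (Protocol article, Data processing and analysis, and Outcomes and data collection): overall level 0.05; three hypotheses at 0.025 each; f = 0.23; power 0.80; 184 before dropout; 30% dropout; 256 recruited in two equal groups; outcomes at two time points; EQ-VAS from two informants. Sidedness is not stated. The hypotheses are worded without direction, so two-sided tests are assumed. Correlations between test statistics are not given and are assumed below.

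**1. The plan's own sample size.** ANCOVA with two groups and one covariate: noncentral F with 1 and N − 3 degrees of freedom and λ = f²N. At level 0.025 the smallest N with 80% power is 183, or 184 with equal groups. At N = 184, λ = 0.0529 × 184 = 9.73 and power is 80.4%. The stated 184 is reproduced, so 0.025 is the level that sized the trial.

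**2. The Bonferroni level.** 0.05/3 = 0.0167. 0.05/2 = 0.025. The stated level is the one for two hypotheses.

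**3. Family-wise error for three tests at 0.025.**
- Upper bound: 3 × 0.025 = 0.075.
- Independent: 1 − 0.975³ = 0.0731.
- Equal positive correlation r, by simulating equicorrelated normal test statistics:

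| r (assumed) | Family-wise error |
|---|---|
| 0.3 | 0.070 |
| 0.5 | 0.065 |
| 0.7 | 0.057 |
| 0.9 | 0.044 |

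For comparison, three independent tests at 0.0167 give 0.0492.

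**4. If the time points and informants are each tested confirmatorily.**
- Six tests (three outcomes, two time points, one EQ-VAS informant): bound 6 × 0.025 = 0.15; independent 1 − 0.975⁶ = 0.141.
- Eight tests (WHODAS 2 + RS-11 2 + EQ-VAS 4): bound 8 × 0.025 = 0.20; independent 1 − 0.975⁸ = 0.183; 0.138 at r = 0.5; 0.106 at r = 0.7; 0.065 at r = 0.9.

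**5. What each level means for the primary outcome.** 256 × 0.70 = 179.2, so 179 remain after 30% dropout.

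| Level for WHODAS at t2 | Evaluable N for 80% power | Power at 184 | Power at 179 |
|---|---|---|---|
| 0.05 | 151 | 87.4% | 86.4% |
| 0.025 | 183 | 80.4% | 79.2% |
| 0.0167 | 201 | 75.8% | 74.5% |

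The gap between 179 and 184 comes from the dropout allowance, which is a separate matter.

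**The case against.** The best defence of 0.025 is that it corrects for the two time points. The preceding sentence does specify an analysis at t1 and at t2, and 0.05/2 is exactly 0.025. On that reading each hypothesis is held at 0.05 (provided only one EQ-VAS informant counts), and the fault would be partly one of wording. But the article ties 0.025 to the three hypotheses and does not mention the time points as the reason. Even if that was the intention, nothing corrects across the three hypotheses, and the bound is 0.15.

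Three limits do stand.

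- A reader might infer that the primary result has an inflated error rate. It does not. WHODAS at 12 months is tested at 0.025, half of what a single primary needs. The inflation concerns claims made across the three hypotheses.
- A reader might infer that the correction buys nothing. It does buy something: three independent tests at 0.05 each would give 1 − 0.95³ = 0.143, against 0.073 at 0.025. Nor does the primary lose planned power, because the 184 was calculated at 0.025.
- A reader might take 0.20 as the trial's error rate. It is an upper bound over eight tests, and the article does not list these as separate confirmatory tests. The same scale six months apart, or from two informants, is probably positively correlated, which lowers the rate.

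A testing order, or the choice of one EQ-VAS informant, may be set out in the full protocol or a statistical analysis plan, so its absence from the article is not the fault. The fault is the rule that the article does state.

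**Conclusion.** The concern holds for the family of three hypotheses. Calling 0.025 a Bonferroni level for three hypotheses at 0.05 is wrong, and neither reading of the sentence controls the three together at 0.05. The family-wise error is at most 0.075; it is 0.073 under independence and about 0.065 at an assumed correlation of 0.5. It falls below 0.05 only near a correlation of 0.9. That is not a safe assumption for different constructs rated partly by different people (proxy WHODAS, self-rated RS-11). The rate is higher if both time points and both EQ-VAS informants are treated as confirmatory: bound 0.20, about 0.14 at r = 0.5.

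The conclusion on the primary outcome is safe, and if anything conservative. All figures assume two-sided tests; the correlated figures also assume equal correlation between all tests.

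**What to change.** Settle the rule before any unblinded analysis, in one of two ways.

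**Preferred: a testing order.** Test WHODAS at 12 months first, alone, at two-sided 0.05. Only if it is significant, test RS-11 and EQ-VAS at 12 months, with one EQ-VAS informant named in advance, by fixed sequence or Holm at 0.05. Report all 6-month results and the other EQ-VAS informant as supportive. Power for the primary at f = 0.23 becomes 87.4% with 184 evaluable and 86.4% with 179. The cost is that secondary claims become conditional on the primary. The primary's level also rises from 0.025 to 0.05 after recruitment has begun, so the change should be dated and justified. Under the article's own amendment rules it needs approval by the funder and the ethics committee and an updated registry entry.

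**Alternative: keep the family of three.** Use 0.0167 for each hypothesis (or Holm), name the time point and the EQ-VAS informant, and restate the power as 75.8% at 184 evaluable or 74.5% at 179. Restoring 80% would take 201 evaluable, or 201/0.70 = 287.1, so 288 recruited in equal groups. Stating the lower power is the more practical course.

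Neither option, applied this way, needs further participants or data.

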**Methods:**

We will conduct a randomized-controlled trial with waiting list design in Hamburg, Germany. Inclusion criteria are diagnosis ICD F70-F79 and exclusion criteria are care level > 3 according to the German Social Code XI or being at the end-of-life. Participants will be block randomized. The intervention consists of advanced practice nurses performing case management, social space analysis, prevention planning, and counseling through four outreach home visits on nutrition, mobility, addiction, and stress. Comparison is usual care. The primary outcome is health status (WHODAS) after 12 months. Secondary outcomes are health-related quality of life (EQ-5D) and resilience (RS-11) after 6 and 12 months. The calculated sample size is 256 with an estimated dropout of 30%. Raters and analysts will be blinded. Analysis will be performed using ANCOVAs.

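### 256 enrolled with 30% dropout leaves 179 analysable rather than 184 (a small shortfall), and 0.025 is the Bonferroni level for two tests, not for the three hypotheses listed

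*Protocol article*

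**What the plan says.** All the figures are in the protocol article, Data processing and analysis.

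- **Effect size and model:** "Based on an effect size of *f* = 0.23 for an ANCOVA". The model takes the outcome at the given time point "as the dependent variable and the baseline value (*t*_0_) as the covariate".
- **Alpha, power and required number:** "a significance level of 0.05 with Bonferroni correction to 0.025, and a power of 0.8, 184 participants have to be recruited".
- **Dropout:** "we estimated a 30% dropout rate due to the complexity of the intervention", among other reasons.
- **Enrolment:** "Therefore, we plan to include 256 people with intellectual disabilities (128 per group) in this study".
- **Multiplicity:** "We are going to test three hypotheses with a Bonferroni adjusted alpha of 0.025 each". The three hypotheses listed concern health status, health-related quality of life and resilience.

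The abstract (Methods) repeats the enrolment and dropout pair: "The calculated sample size is 256 with an estimated dropout of 30" per cent.

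Two other places bear on the point. Outcomes and data collection names one primary outcome, WHODAS 2.0 at 12 months; quality of life and resilience are secondary there. The same section says that nothing more is collected from people who leave the study, while people who stop only the intervention are still followed.

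**The concern.** There are two separate problems.

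**The inflation step.** The enrolment figure is presented as following from 184 and 30%, but it does not. On the protocol's own dropout assumption, fewer people reach the primary analysis than the protocol says it needs.

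**The alpha.** A Bonferroni split of 0.05 over three hypotheses is 0.0167. The level used, 0.025, is the split over two. The direct consequence is a false-positive risk: a p-value of 0.02 on any one of the three would be declared significant under a procedure that does not hold 0.05 across them. The same 0.025 went into the sample size, so correcting the alpha also changes the power. How the power changes depends on which correction is chosen.

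As written, a reader of the results cannot tell which error rate was controlled or what power the primary test had.

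**Working it through.** **Inputs** (Data processing and analysis): f = 0.23, which is d = 2f = 0.46 for two equal groups; two groups and one covariate; alpha 0.025; power 0.80; dropout 30%; enrolment 256.

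**Formula.** Noncentral F power for the ANCOVA group effect, with numerator df 1, denominator df N − 3 and noncentrality λ = f²N. With one numerator df this is equivalent to a two-sided test.

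**Step 1: reproduce 184.** At alpha 0.025, N = 182 gives power 0.799 and N = 183 gives 0.802. The minimum is therefore 183, or 184 with equal arms. At N = 184, λ = 0.0529 × 184 = 9.73 and power is 0.804. The stated 184 reproduces.

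**Step 2: the dropout inflation.**

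- 184/(1 − 0.30) = 262.9, so 263. By arm, 92/0.70 = 131.4, so 132 per arm and 264 in total.
- The common shortcut 184 × 1.30 = 239.2 does not give 256 either.
- 256 × 0.70 = 179.2, so 179 analysable, 5 fewer than 184.
- 1 − 184/256 = 28.1%, the largest dropout that 256 can absorb.

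**Step 3: the alpha.**

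- 0.05/3 = 0.0167; 0.05/2 = 0.025.
- Upper bound on family-wise error at 0.025 each: 3 × 0.025 = 0.075.
- If the tests were independent: 1 − 0.975³ = 0.073.

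**Step 4: power at f = 0.23.** For N = 179, λ = 0.0529 × 179 = 9.47.

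| Alpha for the test | Power, N = 184 | Power, N = 179 | N needed for 0.80 |
|---|---|---|---|
| 0.05 (WHODAS at 12 months alone) | 0.874 | 0.864 | 151 |
| 0.025 (as written) | 0.804 | 0.792 | 183 |
| 0.0167 (three hypotheses in one 0.05 family) | 0.758 | 0.745 | 201 |

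At 0.0167 the enrolment for 30% dropout would be 201/0.70 = 287.1, so 288. The effect detectable with 80% power from 179 is f = 0.244.

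**Step 5: separate the two effects.** The dropout slip at 0.025 moves power from 0.804 to 0.792, about 1.2 points (0.8 of a point below the stated 0.80). Moving from 0.025 to 0.0167 with 179 takes it from 0.792 to 0.745, a further 4.7 points.

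**The case against.** **The shortfall is immaterial.** With 179 analysable and alpha 0.025, the effect detectable with 80% power is f = 0.232, which rounds to the stated 0.23. Values of f from 0.225 to 0.235 give required numbers from 191 down to 175, so the gap of 5 lies within the rounding of the effect size. The protocol also describes its 30% as conservative. All of this stands. The slip should be corrected because the figures are presented as following from one another, but a reader who infers from it that the trial is underpowered goes too far.

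**The power is not 0.74.** A reader might conclude that the design has 74% power instead of 80%. The protocol does not support that unconditionally. It fixes the test level at 0.025, where power is 0.79. The 0.74 arises only if all three hypotheses are kept in one 0.05 family and the alpha is corrected to 0.0167. Because a single primary outcome is named, testing that outcome alone at 0.05 is an equally available correction, and power is then 0.86. This objection stands too.

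**0.025 may reflect two time points.** Splitting 0.05 over 6 and 12 months would also give 0.025. The text does not say this: it attaches 0.025 to the three hypotheses. If time points were counted as well, three outcomes at two times would make six tests, and 0.025 would be further from a Bonferroni level. This objection does not stand.

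**Secondary outcomes need not share the primary's alpha.** That is true as a design choice. But the protocol says it applies a Bonferroni adjustment across the three, so it must either carry the adjustment out correctly or drop the claim.

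**Conclusion.** The point holds as two corrections of unequal weight.

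- **Dropout arithmetic:** 179 analysable against 184 required. It is an error, but a small one, with power 0.79 instead of 0.80 at the stated alpha.
- **Alpha:** 0.025 is not the Bonferroni level for three hypotheses. Family-wise error can reach 0.075 instead of 0.05. This is the material part, and it is first a type I error problem.

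Power with 179 lies between 0.74 and 0.86, depending on whether the three hypotheses share one family or the primary outcome is tested alone. Neither end can be quoted without its condition.

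The figures assume that f = 0.23 is the covariate-adjusted effect for the outcome being tested (the protocol gives one f and does not tie it to an outcome), that arms are equal, and that people lost to the study contribute nothing to the 12-month ANCOVA. The last follows from the rule against further data collection after study dropout, unless missing outcomes are imputed.

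Severity is moderate: the enrolment target can stay, but the decision rule must be settled.

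**What to change.** Keep 256 enrolled. Before any unblinded analysis:

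1. **Correct the alpha sentence** in Data processing and analysis and say which alpha governs. Either
   - test WHODAS at 12 months alone at 0.05, with quality of life and resilience as secondary outcomes outside that error rate (power 0.86 with 179); or
   - test all three hypotheses at 0.0167 (power 0.74 with 179, below the stated 0.80).

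   The first option matches the single primary outcome already named and exceeds the stated power.
2. **Restate the sample size** with the power for the chosen alpha. For the first option: *256 enrolled (128 per group), 30% dropout, 179 analysable; power 0.86 for f = 0.23 at alpha 0.05 for WHODAS at 12 months.* For the second: *power 0.74 for f = 0.23 at alpha 0.0167.*

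The abstract's 256 and 30% can stay, since neither number changes. The register entry was not available, so it needs revising only if it carries the affected alpha or power.

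The cost is a short amendment to the wording and the decision rule. No participants, visits or measurements are added. This matters because the protocol has recruitment ending in January 2023, before the article's publication in February 2023.
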